### Sample size

We used the package ‘SWSamp’ in R 3.0 to calculate the power and minimal sample size for the four-cluster stepped-wedge RCT [35, 36]. Our main outcome is the percentage of pregnant smoking women with whom midwives or OB-GYNs discussed specific smoking cessation strategies. We calculated the sample size needed for a power of .80. Assuming a differential effect 35% (control/V-MIS condition) vs. 60% (PROMISE condition) coverage of addressing smoking during the health consultations [29, 30], and taking into account *α* = 0.05 (2-sided) and a coefficient of variation (CV) between clusters of 0.3, we need 18 professionals in each cluster (region in our case). Since there are three regions, we will need at least 54 midwives/OB-GYNs to complete our questionnaires. We will enrol as many professionals as possible.

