### Randomisation

We will use R 3.0 to randomise the order (step) at which midwifery practices and hospitals will be trained. Within each of the three regions, practices will be randomly allocated to one of the four training steps. Neither professionals nor pregnant women will be blinded to their allocation. The authors will also not be blinded to the allocated arm that participants are in.

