### Outcomes

Table 1 represents an overview of all outcomes collected among professionals and pregnant women/mothers. All outcomes for pregnant women measure their current status. Health status, for example, is measured by asking ‘How healthy do you feel?’ with response options (1) ‘Healthy’, (2) ‘Sometimes healthy, sometimes unhealthy’, and (3) ‘Unhealthy’.

**Table 1 Tab1:** Outcome measures

	Measurements^a^		
**Midwives and OB-GYNs**	T0	T1–T4	T5
Background characteristics	x		
Number of smoking clients seen in past month	x	x	x
% smoking cessation discussed	x	x	x
% specific/individual strategies for smoking cessation discussed	x	x	x
Use of protocol components	x	x	x
Barriers and facilitators of using protocol elements	x	x	x
Transferral of smoking status to post-natal care	x	x	x
Appreciation of PROMISE			x
**Post-natal care and youth health care**	T0	T1	
Background characteristics	x		
Use of protocol components^b^	x	x	
Transfer of smoking status from midwife	x	x	
Transfer of smoking status between post-natal care and youth health care	x	x	
Appreciation of PROMISE		x	
**Pregnant women/mothers**	T0	T1	T2
Background characteristics	x		
Smoking status	x	x	x
Partner’s smoking status	x	x	x
Exposure to environmental smoke	x	x	x
Perceived health status	x	x	x
Self-efficacy	x	x	x
Perceived health effects of smoking	x	x	x
Baby background characteristics		x	
Appreciation of protocol elements		x	x
Use of protocol elements by midwife		x	
Use of protocol elements by post-natal care		x	
Use of protocol elements by youth health care			x

^a^Midwives and OB-GYNs: follow-up at each step (every 2 months); post-natal care nurses and youth health care: before training (T0) and 1 year after training (T1); pregnant women/mothers: after 8 weeks of pregnancy (T0), 2 weeks after delivery (T1), and 6 months after delivery

^b^Motivational interviewing techniques only

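### The minimum of 54 professionals does not follow from the stated four-cluster calculation, which implies 4 × 18 = 72; in that same calculation 54 gives about 71% power, not 80%

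*Protocol article*

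**What the plan says.** All the inputs are in the Sample size section of the protocol article. The aim is a "minimal sample size for the four-cluster stepped-wedge RCT", and the target is explicit: "We calculated the sample size needed for a power of .80". The assumed rates are "35% (control/V-MIS condition) vs. 60% (PROMISE condition) coverage of addressing smoking during the health consultations", with alpha "0.05 (2-sided) and a coefficient of variation (CV) between clusters of 0.3". The result and the total follow: "we need 18 professionals in each cluster (region in our case). Since there are three regions, we will need at least 54 midwives/OB-GYNs". The section closes by saying that enrolment will be as large as possible.

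The word cluster has other meanings elsewhere in the article:

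- Randomisation section: within each of the three regions, "practices will be randomly allocated to one of the four training steps".
- Study procedure, on midwives and OB-GYNs: the order is randomised by practice and stratified by region, and clusters 1 to 4 are the groups trained at successive steps.
- Statistical analyses section: the random cluster effect is the practice.

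There are 23 midwifery practices and 3 hospital departments, so 26 randomised units.

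**The concern.** A per-cluster number from a four-cluster calculation has to be multiplied by four. The article multiplies by three, having relabelled the cluster as a region for that one step. No region crosses over as a unit; each contains practices at all four steps. The stated minimum and the stated power therefore cannot both come from the calculation described. A reader who uses 54 to judge whether the trial met its target would be using a figure that the calculation does not support.

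A smaller point concerns the rates. They are described as "coverage of addressing smoking during the health consultations", while Table 1 lists the percentage with whom cessation was discussed separately from the percentage with "specific/individual strategies for smoking cessation discussed". The second is the primary outcome, and the text does not say plainly which of the two the 35% and 60% describe.

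**Working it through.** **Inputs (Sample size section).** p0 = 0.35, p1 = 0.60, difference 0.25; two-sided alpha 0.05 (z = 1.960); CV = 0.3; I = 4 clusters. The section does not say how many occasions were used, which binomial variance, or to which rate the CV applies. The base case assumes T = 5 occasions, the mean binomial variance, and the CV applied to the control rate:

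- σ² = (0.35 × 0.65 + 0.60 × 0.40)/2 = 0.23375
- τ = 0.3 × 0.35 = 0.105, so τ² = 0.011025

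**Formula.** The standard variance for a cross-sectional stepped wedge (Hussey–Hughes), with fixed time effects and a random cluster effect, where s = σ²/n and n is the number per cluster per occasion:

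Var = I·s·(s + Tτ²) / [(I·U − W)·s + (U² + I·T·U − T·W − I·V)·τ²]

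U is the number of treated cluster-periods, W the sum of squared column totals and V the sum of squared row totals of the design matrix. For four clusters and five occasions U = 10, W = 30, V = 30. The denominator is then (40 − 30)s + (100 + 200 − 150 − 120)τ² = 10s + 30τ². Power = Φ(0.25/SE − 1.960).

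**Step 1: reproduce the 18.**

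- n = 18: s = 0.012986. Numerator 4 × 0.012986 × (0.012986 + 0.055125) = 0.003538. Denominator 0.12986 + 0.33075 = 0.46061. Var = 0.007681, SE = 0.0876, power = Φ(2.853 − 1.960) = **0.814**.
- n = 17: power 0.794, below target.

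So 18 per cluster is the smallest number for four clusters, as stated, and the total is 4 × 18 = **72**.

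**Step 2: put 54 into the same calculation.** 54/4 = 13.5 per cluster, s = 0.017315. Numerator 4 × 0.017315 × (0.017315 + 0.055125) = 0.005017. Denominator 0.17315 + 0.33075 = 0.50390. Var = 0.009957, SE = 0.0998, power = Φ(2.505 − 1.960) = **0.707**.

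**Step 3: vary what the article leaves open.** Five or six occasions, four variance forms (control, PROMISE, mean of the two, or at the average rate), and CV applied to the control, average or PROMISE rate (τ = 0.105, 0.1425, 0.18) make 24 combinations.

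| Four clusters, CV 0.3 | Range over 24 combinations |
|---|---|
| Required n per cluster | 16 to 20 |
| Implied total (× 4) | 64 to 80 |
| Power at 54 in total | 0.64 to 0.74 |

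No combination supports 54 at 80% power.

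**Step 4: does taking regions as the clusters rescue 54?** Three clusters of 18, placed on three of the four sequences, give 0.55 to 0.73 depending on the convention and on which sequence is left empty. It does not.

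**Step 5: practices as clusters.** With 26 clusters (54/26 ≈ 2.1 professionals each), CV 0.3 at practice level and independent waves, 54 gives about 0.72 to 0.81. The value shifts by about one point with the placement of the two practices left over after an even split of 26 over four steps.

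**Step 6: repeated measures on the same people.** With within-person correlation ρ, replace s by (1 − ρ)σ²/n and τ² by τ² + ρσ²/n. The article gives no ρ. For an assumed ρ = 0.3, 54 professionals in the four-cluster layout give about 0.79 to 0.86.

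**The case against.** The strongest reply is that 71% describes a simplified calculation and not the trial. The Primary outcome and Statistical analyses sections describe the same professionals answering six questionnaires, a percentage over all the smoking clients each has seen, and a random effect for the individual. Step 6 shows that a moderate within-person correlation alone can bring 54 back to about 80% or above. With practices as clusters, 54 is borderline even without that correlation. A reader might infer that the trial is underpowered, or that the planned model has 71% power. The documents do not support either: the correlation and the number of clients per professional are not given, and the shortfall can be shown only within the calculation that the article reports. This part of the reply stands, and 71% must be read as conditional.

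It does not repair the arithmetic. The article does not report a repeated-measures or 26-practice calculation, so any agreement of 54 with 80% under such a model would be coincidence.

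Two further replies have some force. The 54 is a number completing questionnaires, so it is already net of non-response, although the article does not say whether that means all six. And enrolment is open-ended, so the actual sample may exceed the minimum; that does not make the stated minimum correct.

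On the rates, a reader might infer that the trial was sized for the wrong outcome. That goes too far. The same section names discussion of specific cessation strategies as the main outcome just before giving the rates, and the sources cited for them are not at hand. The phrase about addressing smoking may simply be loose wording.

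**Conclusion.** The point holds in a limited form. The figure of 18 per cluster is sound for four clusters; the total of 54 is not derived from it. The reported calculation implies 72, and 54 yields about 71% power in it (0.64 to 0.74), against the 80% claimed. The multiplication error needs no modelling assumption. The 71% rests on CV 0.3, a normal approximation, and one independent binary observation per professional per occasion. The power of the planned mixed model at 54 is unknown from the documents and may be higher. The wording of the 35% and 60% is an ambiguity to clear up, not a demonstrated error.

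**What to change.** 1. Delete the parenthesis that equates cluster with region, and the multiplication by three regions.
2. Make total and power agree: give 72 as the minimum for the four-cluster calculation at 80% power, or keep 54 and report about 71% for that calculation, with the variance convention and number of occasions stated.
3. Preferably, replace the calculation with one that matches the design: the 26 randomised practices as clusters, six repeated measures on the same professionals, the within-person correlation stated as an assumption with a range, and a statement of whether the required number means completers of all six questionnaires. This is better than step 2 alone, because a four-cluster calculation does not describe the units that are randomised.
4. State whether 35% and 60% are rates for specific strategies discussed or for any discussion of smoking; if the latter, give the rates assumed for the primary outcome.

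The cost is a corrected paragraph and a short recalculation. Randomisation, outcome and analysis model stay as they are, and enrolment was already open-ended. The only drawback is that the stated figure may look less favourable.

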### Control condition: V-MIS protocol

All participating midwifery practices and hospitals start in the control condition and will use the V-MIS protocol (usual care), for which they have already been trained in the past. The V-MIS protocol consists of seven consecutive counselling steps in which midwives and their clients discuss smoking cessation. Depending on their client’s motivation to quit smoking, midwives could take multiple steps in a single visit. While these counselling steps could best be conducted in consecutive order, deviations are allowed (e.g. going back a step). Figure 2 provides an overview of the counselling steps of the V-MIS protocol. A more extensive description of the V-MIS protocol can be found elsewhere [28].

**Fig. 2 Fig2:**
[figure not shown]
Counselling steps of the V-MIS protocol for smoking cessation care among pregnant women

#### Step 1: Determine smoking behaviour and underlying motivations

Midwives assess their client’s smoking status, number of cigarettes per day, and whether the client is motivated to quit within 30 days. Smoking status is registered in the online system.

#### Step 2: Increase motivation to quit

If a client is not motivated to quit smoking, midwives use motivational interviewing techniques to strengthen their client’s intrinsic motivation to quit smoking. They also discuss short-term advantages of quitting and disadvantages of smoking.

#### Step 3: Discuss barriers of quitting and ways of mobilising support

If a client is motivated to quit, midwives discuss barriers to successful quitting. Together, the client and midwife discuss how to mobilise social support for quitting.

#### Step 4: Set a quit date

Together, the midwife and client set a quit date. Midwives register the quit date in the client’s records and discuss the quit attempt during the next session.

#### Step 5: Provide and discuss self-help materials

While setting a quit date, the midwife and client discuss whether the client needs additional support. Midwives may provide self-help materials or refer the client to a specific type of behavioural support (i.e. telephone counselling, personal coaching, or group counselling). The use of nicotine replacement therapy is not encouraged in the Netherlands among pregnant women and may only be used among specific groups of heavy smokers [24].

#### Step 6: Provide after care, if needed

If a client has quit smoking, midwives continue to discuss smoking (cessation) in the following visits in order to prevent relapse. They discuss past moments of craving and ways to deal with them. If a client has relapsed, midwives try to motivate their client to quit smoking again.

#### Step 7: Provide support and help preventing relapse after delivery

Midwives could help prevent relapse after delivery by discussing this beforehand with their clients. In the last stages of pregnancy, the client and the professional discuss which barriers and difficult situations the client may encounter. The midwives stimulate their client to develop strategies for overcoming these barriers. They also discuss the dangers of second-hand smoke to the baby.

### Experimental protocol: PROMISE

Those switched to the experimental condition will start using the PROMISE protocol. The PROMISE protocol consists of both the original V-MIS protocol (including its seven steps) and additional elements designed to save consultation time and to increase counselling effectiveness. The content of the seven steps has been made more suitable to pregnant women with low SES or functional health illiteracy.

#### Carbon monoxide meters

We added the use of carbon monoxide (CO) measurements to steps 1 and 6 of the V-MIS protocol. A carbon monoxide meter measures the CO level in someone’s expired air and can be used to determine smoking status during pregnancy [37]. While CO levels continue to be elevated for at least 24 h after smoking a cigarette, CO meters are able to determine smoking status even if someone abstained from smoking a few hours prior to measurement. CO measures offer a non-invasive way to show pregnant women how much CO potentially reaches her unborn child. CO measurements are mandatory in smoking cessation care for pregnant women in some countries [38], but they are rarely used in Dutch midwifery practices. This study is the first one to explore the use of CO measurements among pregnant women in the Netherlands.

We will train midwives to use the CO measurement as a conversation starter and to avoid using the measurement outcome in a disapproving or criticising way. They will use it to stimulate smoking cessation (step 1) or staying smoke free (step 6). We will provide specific PROMISE score forms illustrating how CO and nicotine from cigarettes reach the unborn baby. Midwives could use this to communicate the health effect of smoking to women with functional health illiteracy. In line with previous research [37], midwives will be trained to use a cut-off point of 4 part per million to identify smokers among their clients.

#### Storyboard leaflets

We developed storyboard leaflets to help midwives enhance motivation among women with functional health illiteracy (steps 2 and 3), to guide these women towards smoking cessation (step 5), and to prevent relapse after quitting (step 6). Storyboard leaflets are visual stories, accompanied by a small text. By using simple texts and illustrations, information can be made accessible and comprehensible to both people with either poor or good literacy skills [39]. Storyboard leaflets stimulate doctor-client communication and have proven useful in other health-related domains, such as diabetes and obesity [40, 41]. They may be used for counselling for both people with poor literacy skills and for people with good literacy skills [40].

In an exploratory study, we interviewed 23 pregnant women (of whom most had a low SES) and asked them to help developing the story line for the leaflets. Their feedback made the texts and illustrations highly suitable for women with poor functional health literacy skills. Based on the target group’s feedback, we developed three versions of the same storyboard: one for pregnant women with a partner, one for pregnant women without a partner, and one for women who recently gave birth (see Fig. 3 for example images). Midwives will use the first two versions; post-natal care nurses and youth health care professionals will use the third one.

**Fig. 3 Fig3:**
[figure not shown]
Example pages from a PROMISE storyboard leaflet

#### Referral to smoking cessation support

In the original V-MIS protocol, midwives were only able to refer clients to intensive smoking cessation counselling in step 5. In the PROMISE protocol, they will be able to do so from step 2 onwards. By allowing them to refer women earlier on in the protocol, they are able to help clients even if they lack time to counsel them themselves. As midwives are the main care provider for pregnant women, we will stress that midwives should only refer clients if they see no other option. To stimulate the use of the referrals in such cases, we developed an online list of local referral options for each of the three regions (a social map).

#### Relapse prevention: post-natal care and youth health care

Since most women who quit smoking during pregnancy relapse after delivery [9, 20, 32], relapse prevention is extremely important. Unexpected stress factors may arise after delivery and could increase the chance of relapse [42]. While midwives and OB-GYNs visit their clients 1–3 times after delivery, relapse prevention has been a small part of the original V-MIS protocol. Post-natal care nurses spend more time with clients after delivery (8 days, 3–10 h per day), and mothers visit the youth health care clinic about 15 times in the first 4 years of their children’s life. Both post-natal care nurses and youth health care therefore play an important role in guiding new mothers and preventing relapse after childbirth.

Although both types of professionals do not influence the main study outcome, we felt a strong moral obligation to help these professionals too and to allow continued smoking cessation support after delivery. This is why post-natal care nurses and youth health care professionals will be offered both a face-to-face training and a counselling manual too. Contrary to the training and manual for midwives, their training and manual will be focussed at preventing relapse after delivery (instead of stimulating smoking cessation). We also developed specific storyboard leaflets about remaining smoke free after delivery. Post-natal care nurses and youth health care professionals could use this to support young mothers in remaining abstinent.

To further stimulate cooperation between midwives, OB-GYNs, post-natal care nurses, and youth health care, we developed a new transferring document. Health professionals could use this form to exchange information about the smoking status and smoking cessation.

#### Face-to-face training and counselling manual

To stimulate the correct use of the PROMISE protocol, all midwives, OB-GYNs, post-natal care nurses, and youth health care professionals will be offered a comprehensive face-to-face training. Although some midwives and OB-GYNs might have received a training in the V-MIS protocol years before this study, the materials used in that training were outdated. That is why we developed a new training with newer materials.

The training for midwives and OB-GYNs will consist of four parts. First, they receive background information about smoking cessation and the PROMISE protocol. Next, they will receive background information about people with functional health illiteracy. This section includes ways of recognising whether a client has poor literacy skills and techniques for communicating with them. One such technique is the teach-back method, in which a health professional checks whether a client understands the professional’s recommendations by asking the client to summarise the professional’s recommendations in their own words [43]. Third, we will teach motivational interviewing techniques to strengthen communicating with low SES and functionally illiterate women and their partners [44]. Participants will practice example conversations and discuss past challenging conversations with clients. Finally, participants will be trained in using the carbon monoxide meter.

The training for post-natal care nurses and youth health care professionals will only include the background information and the motivational interviewing techniques. Both post-natal care nurses and youth health care professionals will not use the carbon monoxide meter. By leaving out information about low health literacy, we avoid making the post-natal care nurses uncomfortable, as they often have poor literacy skills themselves.

All training participants will receive a comprehensive counselling manual. This manual discusses the V-MIS counselling protocol and the elements we added. It provides information about people with poor functional health literacy skills and ways of using the carbon monoxide meter. It includes a large number of example conversations about common barriers, difficult situations, withdrawal symptoms, and ways of mobilising social support. All example conversations are based on motivational interviewing techniques. We have developed three manuals: one for midwives and OB-GYNs, one for post-natal care nurses, and one for youth health care.

### Outcomes

Table 1 represents an overview of all outcomes collected among professionals and pregnant women/mothers. All outcomes for pregnant women measure their current status. Health status, for example, is measured by asking ‘How healthy do you feel?’ with response options (1) ‘Healthy’, (2) ‘Sometimes healthy, sometimes unhealthy’, and (3) ‘Unhealthy’.

**Table 1 Tab1:** Outcome measures

	Measurements^a^		
**Midwives and OB-GYNs**	T0	T1–T4	T5
Background characteristics	x		
Number of smoking clients seen in past month	x	x	x
% smoking cessation discussed	x	x	x
% specific/individual strategies for smoking cessation discussed	x	x	x
Use of protocol components	x	x	x
Barriers and facilitators of using protocol elements	x	x	x
Transferral of smoking status to post-natal care	x	x	x
Appreciation of PROMISE			x
**Post-natal care and youth health care**	T0	T1	
Background characteristics	x		
Use of protocol components^b^	x	x	
Transfer of smoking status from midwife	x	x	
Transfer of smoking status between post-natal care and youth health care	x	x	
Appreciation of PROMISE		x	
**Pregnant women/mothers**	T0	T1	T2
Background characteristics	x		
Smoking status	x	x	x
Partner’s smoking status	x	x	x
Exposure to environmental smoke	x	x	x
Perceived health status	x	x	x
Self-efficacy	x	x	x
Perceived health effects of smoking	x	x	x
Baby background characteristics		x	
Appreciation of protocol elements		x	x
Use of protocol elements by midwife		x	
Use of protocol elements by post-natal care		x	
Use of protocol elements by youth health care			x

^a^Midwives and OB-GYNs: follow-up at each step (every 2 months); post-natal care nurses and youth health care: before training (T0) and 1 year after training (T1); pregnant women/mothers: after 8 weeks of pregnancy (T0), 2 weeks after delivery (T1), and 6 months after delivery

^b^Motivational interviewing techniques only

